# Efficacy and Safety of Haidebao Body Lotion in Patients With Mild Atopic Dermatitis: Protocol for a Multicenter, Double-Blind, Randomized, Placebo-Controlled Trial

**DOI:** 10.2196/71255

**Published:** 2025-06-10

**Keywords:** atopic dermatitis, emollient, randomized controlled trial, study protocol, double blind, double-blind

## Abstract

**Background:**

Atopic dermatitis (AD) is a chronic, relapsing skin condition that significantly impacts patients’ quality of life. In clinical practice, AD is commonly managed through the use of emollients and topical corticosteroids. Haidebao Body Lotion (HBL) incorporated with calcium-based antimicrobial peptide compounds (CAPCS) has demonstrated clinical benefits for patients with mild AD, but there is a lack of high-quality clinical trial evidence.

**Objective:**

In this study, we will implement a multicenter, double-blind, randomized, placebo-controlled trial to evaluate the efficacy and safety of HBL incorporated with CAPCS as an adjunctive therapy in ameliorating mild AD.

**Methods:**

This multicenter, double blind, randomized, placebo-controlled trial will recruit 200 eligible participants from 10 hospitals in China from October 2023 to October 2025. In this study, AD will be confirmed in accordance with Williams diagnostic criteria, and patients with mild AD, aged 18-55 years, who provide signed informed consent will be enrolled. However, patients who are pregnant, have serious underlying diseases, have communication barriers, and violate medication regulations will be excluded. The 200 patients will be randomly assigned (1:1) to a treatment group (HBL with CAPCS; n=100, 50%) and a control group (HBL without CAPCS, placebo; n=100, 50%), and each participant will receive 3 sessions of treatments per day for 4 weeks. The primary outcome is the proportion of patients who achieve at least 60% improvement in the Eczema Area and Severity Index (EASI) score from baseline to week 2. The secondary outcomes include the Numeric Rating Scale (NRS), EASI50, EASI60, and Dermatology Life Quality Index (DLQI) scores at weeks 2 and 4, as well as adherence and adverse events. The full analysis set (FAS) and the per protocol set (PPS) will be analyzed using SAS 9.3 software, and missing data will be processed using the multiple imputation method. In this study, *P*<.05 is considered statistically significant.

**Results:**

Participant recruitment began in January 2024. As of May 2025, we enrolled 180 patients, with 160 (88.9%) completing the 2-week follow-up. Data collection and management are still ongoing, and data analysis has not yet been performed.

**Conclusions:**

This study will evaluate the clinical efficacy and safety of HBL incorporated with CAPCS in the treatment of patients with mild AD. If treatment efficacy is proven, HBL incorporated with CAPCS could be clinically used as an adjunctive therapy in ameliorating mild AD.

**International Registered Report Identifier (IRRID):**

DERR1-10.2196/71255

## Introduction

Atopic dermatitis (AD) is a chronic, recurrent, inflammatory skin condition that affects approximately 11%-20% of children and 5%-8% of adults [1,2]. AD often begins in infancy, with approximately 50% of cases occurring before the age of 1 year [3]. AD usually exhibits a chronic course, occasionally protracts into adulthood, and is distinctly characterized by acute erythema featuring vague borders, accompanied by edema, blisters, and oozing blood [4]. In the chronic phase of AD, there is thickening of the skin, particularly in areas such as the cheeks, arms, and flexor surfaces of the trunk, which can result in sleep disturbances, severe life quality interference and daily activity deprivation, and the loss of psychological well-being [5,6]. AD is often associated with other allergic conditions, such as asthma and food allergies, and it may also increase the risk of nonallergic comorbidities, including various autoimmune or immune-mediated disorders, and psychiatric illnesses [7]. The persistent relapsing trajectory, elevated comorbidity rate, substantial economic burden, and involvement of the entire family in the treatment process have significantly reduced the quality of life of patients with AD and their family members [8,9].

The pathogenesis of AD is complex, involving genetic susceptibility, microbiome effects, environmental factors, and immune dysregulation [10]. Anti-inflammatory agents, phototherapy, wet-wrap therapy, systemic immunosuppressants, and short-term systemic steroid treatment are used to manage persistent or severe cases of AD [11]. However, use of the aforementioned local and systematic AD treatments often fails to provide long-term disease control due to safety concerns. Previous studies indicate that oral corticosteroids can ameliorate AD lesions, but the disease may flare up again if these medications are discontinued [12]. Moreover, topical steroids may cause side effects, involving skin thinning, lines, acne, cataracts, glaucoma, and delayed growth in children [13]. The use of antihistamines may lead to an increase in attention deficit hyperactivity disorder (ADHD) in children [14]. These side effects induced by local or systematic treatments restrict prolonged application of antihistamines in patients with AD.

The external application of moisturizing emollients is the basis for AD treatment, which can not only improve cuticle hydration and reduce inflammation [15] but also repair the damaged skin barrier, decrease the stimulation of external factors, and, thus, reduce the attack frequency and disease severity [16]. In patients with mild AD, continuous, frequent, and heavy use of emollients is recommended to maintain skin barrier function, even in the absence of lesions [17]. In recent years, the development of new active ingredients has led to the widespread clinical application of emollients to improve the skin barrier, with reparative, anti-inflammatory, and moisturizing effects, especially in patients with mild AD [18,19].

Calcium-based antimicrobial peptide compounds (CAPCS) consist of naturally occurring active calcium and a variety of antibacterial peptides (AMPs) derived from farmed marine shellfish. Previous studies indicate that active calcium can enhance capillary wall density, reduce capillary permeability and exudation, and safeguard the integrity of cell membranes. Simultaneously, active calcium can inhibit the release of inflammatory mediators and exhibit anti-inflammatory and anti-allergic properties. Previous studies indicate that calcium exists in the human body in the form of calcium ions. Calcium ions and their concentration gradients in the epidermis play a crucial role in regulating various skin functions, including keratinocyte differentiation, skin barrier formation, and permeability barrier homeostasis [20]. G protein–coupled receptors (GPCRs), which are widely expressed in mammals, are associated with skin pruritus through their signaling pathways. So, calcium ions can bind to G proteins, thereby inhibiting their activity and alleviating pruritus [21]. Moreover, the AMPs in CAPCS can alter bacterial cell membrane permeability, creating openings that allow calcium ions to rapidly enter the cells. This influx of calcium ions raises intracellular calcium levels, causing metabolic disruption and organelle leakage, ultimately leading to the death of pathogenic bacteria [22]. Additionally, AMPs can prevent bacterial infections, alleviate skin inflammatory responses, and thereby further improve patient symptoms [23]. Previous experimental studies indicate that CAPCS have therapeutic effects on AD, with similar efficacy as desonide cream (a weak corticosteroid) in controlling scratching and relieving itching in mice [24]. Haidebao Body Lotion (HBL) incorporated with CAPCS has also demonstrated clinical benefits for patients with mild AD, but there is a lack of high-quality clinical trial evidence. Therefore, this study aims to evaluate the treatment efficacy and safety of HBL incorporated with CAPCS in patients with mild AD.

## Methods

### Study Design

This study is a multicenter, double-blind, randomized, placebo-controlled clinical trial that will be conducted in 10 tertiary hospitals in China from October 2023 to October 2025. The 10 hospitals are the Shanghai Skin Diseases Hospital, the Third Hospital affiliated to Chongqing Medical University, the First Hospital of Hangzhou, the Third Hospital affiliated to Peking University, the First Hospital of Fujian Medical University, the Skin Diseases Hospital affiliated to South Medical University, the First Hospital of Wuhan, the First Hospital affiliated to Kunming Medical University, the Skin Diseases Hospital of Jiangxi, and the First Hospital affiliated to Anhui University of traditional Chinese medicine. In this study, patients with mild AD who provide signed informed consent will be randomly assigned (1:1) to a treatment group (HBL with CAPCS) and a control group (HBL without CAPCS, or placebo). This study is registered with the Chinese Clinical Trial Registry (ChiCTR2400087274).

### Sample Size

In this study, the sample size was calculated based on the proportion of patients achieving at least 60% improvement (defined as the effective rate) in the Eczema Area and Severity Index (EASI) score from baseline to week 2 (EASI_60_) in both the treatment group and the control group. A previous pilot study (data not published) indicated that the proportion of EASI_60_ achievement at week 2 was 50% in the CAPCS group and 20% in the placebo group. In addition, a previous open-label clinical trial involving 60 pediatric patients with AD demonstrated comparable efficacy outcomes, with CAPCS combination therapy showing a 42.86% response rate versus 7.14% for the control group at week 2, with statistically significant differences (*P*<.05) [25]. In this study, we used the following formula to calculate the sample size:

We set the proportion of EASI_60_ achievement at week 2 in the treatment group to p1=45%, the proportion of EASI_60_ achievement at week 2 in the control group to p2=20%, the type I error to α=0.05, the type II error to β=0.1. The sample size calculation indicated that at least 70 patients be recruited in each group. Considering a 20% dropout rate and a 10% multicenter effect, we plan to enroll 100 patients with mild AD in each group, for a total of 200 patients with mild AD.

### Participants

In this study, AD will be confirmed in accordance with Williams diagnostic criteria [26], and patients with AD will be recruited and screened from 10 tertiary hospitals in China from October 2023 to October 2025 by publishing recruitment announcements in newspapers or on information platforms of the hospital official websites, display boards outside the clinics, and information counters. All patients are required to sign informed consent forms before the study begins.

In this study, patients will be included if they meet the inclusion criteria as follows: (1) diagnosis of AD according to Williams diagnostic criteria, (2) age 18-55 years for both males and females, (3) a target lesion with a diameter of 2-10 cm located on the limbs or the trunk, (4) EASI score<6, and (5) skin area<5% body surface area before treatment. The exclusion criteria are as follows: (1) pregnant or lactating women; (2) patients who have undergone AD system treatment within 3 months or local treatment or phototherapy within the past 2 weeks at the time of recruitment; (3) patients with serious systemic diseases or disorders of the heart, lungs, liver, or kidneys or mental illness; (4) patients who are allergic to calcium supplements; (5) patients with systemic disease or an active skin condition (eg, psoriasis) that affects the evaluation; (6) patients with scars, birthmarks, tattoos, freckles, etc; (7) patients with bacterial, viral, or fungal infections requiring anti-infective therapy; (8) patients who have participated or are currently participating in clinical trials of other drugs within the past month; and (9) patients with communication barriers, unable to complete the questionnaire.

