### Intervention and Control

#### Treatment Group

Patients with mild AD in the treatment group will undergo 3 treatment sessions with HBL incorporated with CAPCS every day for 4 weeks. To ensure the correct application of HBL, we will provide individual guidance to each patient, instructing them that 1 knuckle length of HBL should be used to cover no more than 2% of the body surface area and to apply a 3-5-minute finger massage to promote its absorption. In this study, patients will also be instructed not to use any additional treatment for AD. If a patient uses additional treatment for an emergency, detailed information will be recorded and the patient will be asked to withdraw from the trial.

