#### Control Group (Placebo)

Patients with mild AD in the control group will undergo 3 treatment sessions with the placebo (HBL without CAPCS) every day for 4 weeks. The HBL placebo is produced and provided by Shell Party Innovations Technology (Shenzhen) Co, Ltd, which maintains complete consistency in HBL in terms of appearance, weight, color, odor, and package, except for the incorporation of CAPCS (Figure 1). The application, individual guidance, and instruction regarding HBL placebo use in the control group will be completely in line with that in the treatment group. Patients in the control group will also be instructed not to use any additional treatment for AD. Like before, if a patient uses additional treatment for an emergency condition, detailed information will be recorded and the patient will be asked to withdraw from the trial.

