## Discussion

### Summary

AD is an autoimmune inflammatory skin disease that can last for a lifetime [33]. AD usually exhibits a chronic course, with thickening of the skin, sleep disturbance, severe life quality interference, and daily activity deprivation, which not only causes physical pain for the patient but also imposes heavy social and economic burdens on them [34,35]. For AD treatment, anti-inflammatory agents, wet-wrap therapy, systemic immunosuppressants, and short-term steroid treatment are used to manage persistent or severe AD cases [11]. However, the use of local and systematic treatment often fails to provide long-term disease control due to safety concerns. As adjuvant therapy, the external application of moisturizing emollients is the basis for AD treatment, which can not only improve the hydration of the cuticle and reduce inflammation [15] but also repair the damaged skin barrier, decrease the stimulation of external factors, and reduce the attack frequency and disease severity [16]. In recent years, the development of new active ingredients has led to the widespread clinical application of emollients to improve the skin barrier in patients with AD.

CAPCS, as new active ingredients, are derived from farmed marine shellfish. Previous studies indicate that the active calcium in CAPCS can inhibit the release of inflammatory mediators and exhibit anti-inflammatory and anti-allergic properties. Moreover, HBL incorporated with CAPCS has similar therapeutic effects as desonide cream in scratch control and itching alleviation in mice and in patients with AD [21], but there is a lack of high-quality clinical trial evidence. This protocol outlines the basic principle and design of a multicenter, double blind, randomized, placebo-controlled trial with 200 patients with mild AD in China. We plan to evaluate the treatment efficacy and safety of HBL incorporated with CAPCS in the enrolled patients, which is expected to yield more generalizable evidence due to the diversity in geography, climate, and participants from the 10 selected hospitals. To the best of our knowledge, this is the first multicenter clinical trial that will recruit 200 patients with AD to evaluate the treatment efficacy and safety of HBL incorporated with CAPCS in China. The clinical data of patients with AD will be extracted from the health information system (HIS) directly without recall bias, resulting in high data quality.

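### Exclusion criterion 4 covers allergy to the calcium in CAPCS but not to its shellfish-derived peptides, a minor precautionary gap

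*Protocol article*

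**What the plan says.** The Participants section of the protocol article numbers nine exclusion criteria. The only one that concerns allergy is "4) patients who are allergic to calcium supplements". The shorter list in the Abstract adds no other.

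The Introduction describes CAPCS as active calcium together with "a variety of antibacterial peptides (AMPs) derived from farmed marine shellfish", and the Discussion (Summary) repeats the origin: "CAPCS, as new active ingredients, are derived from farmed marine shellfish". On the patient population, the Introduction says "AD is often associated with other allergic conditions, such as asthma and food allergies".

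Patients in the treatment group "will undergo 3 treatment sessions with HBL incorporated with CAPCS every day for 4 weeks" and are told to "apply a 3-5-minute finger massage to promote its absorption". The placebo matches the active lotion "except for the incorporation of CAPCS", so only the active arm meets the shellfish-derived material.

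**The concern.** By excluding patients allergic to calcium supplements, the sponsor appears to have accepted that allergy to a constituent of the active ingredient is a reason not to randomize. The criterion then stops at one of the two constituents that the article names. Criteria 3 and 5, on serious systemic disease and on conditions that affect the evaluation, do not plainly reach a known food allergy. A site that follows the list can enroll such a patient.

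What is at stake is a precaution for that patient, not the trial's inference. The lotion would be massaged in several times a day on skin for which the Introduction gives one purpose of emollients as to "repair the damaged skin barrier". Investigators are blinded, so after randomization they cannot steer the patient away from the active lotion. Eligibility is the point at which prevention needs no unblinding.

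**Working it through.** **1. Constituents against the criterion**

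| Stated constituent of CAPCS | Covered by an exclusion? |
|---|---|
| Active calcium | Yes, criterion 4 |
| Peptides derived from marine shellfish | No, in none of the nine |

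**2. Chance of active lotion.** The Randomization section gives 100 of 200 patients to each arm: 100/200 = 50%.

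**3. Exposure of one active patient.** Three applications a day for 28 days: 3 × 28 = 84, of which 3 × 14 = 42 fall before the week 2 visit. Eligibility limits the affected skin to under 5% of body surface.

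**4. Patients that a change could still reach.** The Results section gives 180 enrolled between January 2024 and May 2025, with recruitment planned to finish by July 2025.

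- Accrual rate: 180/17 = 10.6 to 180/16 = 11.25 a month.
- Left at the May 2025 status: 200 − 180 = 20, taking 20/11.25 = 1.8 to 20/10.6 = 1.9 months, in line with the July end.
- The article is dated 10 June 2025. May status to that date is 10 to 40 days, about 0.33 to 1.31 months.
- Left at publication: 20 − 11.25 × 1.31 = 5.3 to 20 − 10.6 × 0.33 = 16.5, about 5 to 16.
- Left after one further month for ethics reporting and roll-out to 10 hospitals: 5.3 − 11.25 is below zero, so 0; 16.5 − 10.6 = 5.9. About 0 to 6.

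**5. Patients on treatment at any time while recruitment runs.** Rate × 28/30.44 = 9.7 to 10.3, about 10.

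**6. Patients with such a history.** The article gives no prevalence of shellfish allergy, so 2% to 10% is an assumption.

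| Group | Number | With a history at 2% to 10% |
|---|---|---|
| Left to recruit at publication | 5 to 16 | 0.1 to 1.6 |
| Left after one month | 0 to 6 | 0 to 0.6 |
| On treatment at any time | about 10 | 0.2 to 1.0 (active half 0.1 to 0.5) |

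These count allergy histories, not reactions. No reaction rate can be derived from the article.

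**7. Effect on the design.** None. An excluded patient is replaced, so the target of 100 per group stands. That target agrees with the plan's own 70 per group and its combined 30% allowance: 70/(1 − 0.30) = 100.

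**The case against.** The strongest objection is that no hazard is shown. The article does not call shellfish allergy a contraindication, does not say which shellfish are used or whether allergenic protein survives processing, and speaks of food allergies in general. That stands. A reader might infer that the protocol exposes allergic patients to a known danger, or that anyone on treatment with such a history should be stopped. The documents support neither. A patient already using the lotion has shown some tolerance, and half of those asked are on placebo.

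The second objection is that safeguards exist. Risks are explained before consent and dermatologists treat adverse events (Adverse Events). Medical history is taken at enrollment and at weeks 2 and 4 (Table 1). Patients are contacted during follow-up (Quality Control) and may withdraw at any time. A dermatologist administers the intervention (Randomization), and itch is scored before and at 1, 5, 10, 15 and 30 minutes after the baseline application (NRS Score). The consent form is not shown and may mention shellfish. All this lowers the concern, and the itch scoring might pick up an early reaction. It does not answer the point about eligibility: none of these measures makes the patient ineligible, most act after exposure has begun, and itch scoring would not catch every delayed reaction.

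The third objection is timing, and it largely stands. A reader might count all 20 places open at the May 2025 status as reachable. By publication some had probably been filled, and two months after the May status none would be left at the observed pace.

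**Conclusion.** The point holds as a minor, precautionary gap in the wording. Criterion 4 names one of two stated constituents, and a patient with known shellfish allergy is eligible with a 50% chance of active lotion. The size of any risk is unknown and cannot be computed from the article.

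The practical reach is about 5 to 16 new patients from publication, or about 0 to 6 after a month of roll-out. This assumes steady accrual and a July 2025 end. The Abstract and Methods also give October 2025 as the end of the study and recruitment period, so slower accrual would leave more patients within reach. The primary estimate, power and type I error are untouched.

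**What to change.** 1. For any patient still to be recruited, and for any later use of this protocol, reword criterion 4 to: *known allergy to calcium supplements, shellfish or any component of the lotion*.
2. For patients on treatment, ask about shellfish allergy at the next planned visit or contact. If the answer is yes, the investigator, still blinded, weighs it together with tolerance so far. History alone is not a reason to stop. Anyone who stops keeps the week 2 and week 4 visits and stays in the full analysis set.

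The cost is a one-line amendment reported to the ethics committee and sent to 10 hospitals, plus one question to about 10 patients. At the assumed 2% to 10%, at most 1 to 2 otherwise eligible patients would be excluded and replaced, and at most about one patient on treatment would need the investigator's judgment.

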### Randomization and Allocation Concealment

In this study, the block randomization method with a random combination of block lengths 4 and 6 will be used to assign the 200 patients with mild AD (1:1) to the treatment group (HBL with CAPCS; n=100, 50%) and the control group (HBL without CAPCS, placebo; n=100, 50%). Independent statisticians will use the entire randomization feature of SAS (SAS Institute) to construct 200 unique computer-generated random sequences for subsequent block randomization. The random numbers printed for participants will be placed in a light-resistant envelope and managed by a third party (not the investigators). If a patient is eligible after the baseline assessment and has provided informed consent, the clinical research coordinator will call the third party to obtain the patient’s random number and finish the group assignment. Next, a dermatologist will administer the corresponding intervention to the patient.

